### Study procedures

Information is also in the Consort diagram (figure 1) and table 2 (screening and data collection).

**Table 2 BMJOPEN2015008622TB2:** Screening and data collection across the trial: summary of the key trial processes from receipt of the invite reply from the potential participant to the data collection time points

CRF	Completed by	Database	Preconsent	Baseline	3 m	6 m	12 m	Ongoing or during treatment	Ref
Invite reply	P	RT	X						na
Screening Questionnaire	P/TT	M	X						na
Consent	P	R		X					na
Sample requisition form	RN	RT		X					na
Adverse events form	TT	M						X	na
Drop-out event form	TT	M						X	na
Note review form	TT	M					X		na
IBS-SSS	P	R		X	X	X	X		23
WASAS	P	R		X	X	X	X		24
SGA	P	R			X	X	X		25
EQ5D	P	R		X	X	X	X		26
Patient enablement	P	R			X	X	X		27
Hospital Anxiety and Depression Scale	P	R		X	X	X	X		28
Client Service Receipt Inventory	P	R		X	X	X	X		29
Cognitive Scale CG-FBD	P	R		X	X	X	X		30
B-IPQ for IBS	P	R		X	X	X	X		31
IBS Behavioural Responses Questionnaire	P	R		X	X	X	X		32
BES	P	R		X	X	X	X		33
“Impoverished Emotional Experience (IEE)” factor of the Emotional Processing Scale-25	P	R		X	X	X	X		34
PANAS	P	R		X	X	X	X		35
Demographics	P	R		X					na
About your IBS	P	R		X					na
Safety questions	P	R			X	X	X		na
Rating of satisfaction	P	R			X	X	X		22
Thoughts on my treatment	P	R			X	X	X		36
Therapist database	T	MT						X	na

BES, Beliefs about Emotions Scale; B-IPQ, Brief Illness Perception Questionnaire; CG-FBD, Cognitive Scale for Functional Bowel Disoders; CRF, Case Report Form; IBS, Irritable bowel syndrome; IBS-SSS, IBS Symptom Severity Score; M, MACRO Clinical Trials Unit database; MT, MACRO Therapist database; na, not significant; P, patient; PANAS, Positive and Negative Affect Schedule; SGA, Subject's Global Assessment of Relief; R, LifeGuide Regul8; RN, Research Nurse/Phlebotomist; RT, Research Team database; T, therapist; TT, trial team; WASAS, Work & Social Adjustment Scale.

**Figure 1 BMJOPEN2015008622F1:**
[figure not shown]
Consort diagram for Assessing Cognitive behavioural Therapy in Irritable Bowel (ACTIB).

Those responding to the recruitment invitation letter will be contacted by the study team to complete a screening process consisting of the Rome III criteria, and questions about exclusion and inclusion criteria to check if they fulfil the eligibility criteria for the study. They will be identified with a unique ID number. Any patient indicating they may have a ‘red flag’ symptom that would indicate the need for further investigations (ie, unexplained weight loss or rectal bleeding) will be referred back to their GP for further assessment and will not enter the study unless the GP feels the symptoms have been fully assessed and that the patient is suitable for study entry.

Those fulfilling the screening entry requirements will be contacted by one of the research team to make sure they are fully informed of trial procedures, and they will be sent the login and access details for the website in order for them to complete an on-line consent form. They will then be sent arrangement details to have a blood test for full blood count, tissue transglutaminase antibodies and C reactive protein (CRP), to exclude alternative diagnoses, such as anaemia that requires further investigation and coeliacs disease (as recommended for IBS diagnosis in the NICE guidelines^4^). The blood tests will be undertaken by practice nurses/GPs within the GP surgeries or by phlebotomists/research nurses at the secondary care sites. Samples will be sent to University Southampton Hospital pathology laboratory for testing and will then be destroyed. The results will be made available to the participants’ GP. If the blood tests are within normal limits, the participant can complete the baseline measures and can then be randomised. If the blood tests show an abnormal result, that is, a CRP over the normal laboratory range, anaemia or a positive test for coeliacs disease, the patient will not be randomised to the trial but will be referred back to his or her GP for further assessment.

### Randomisation

Randomisation will be provided by an independent randomisation service at the UKCRC registered King’s Clinical Trials Unit (CTU) and accessed by study sites via a web-based system. Randomisation will be at the level of the individual, using block randomisation with randomly varying block sizes, stratified by centre (Southampton GP practices, Southampton secondary care, London GP practices, London secondary care). Confirmation emails will be generated automatically and sent to relevant study site and coordination staff.

### Data collection

Research data will be entered onto GCP compliant online data entry systems at CTU (InferMed MACRO) and Regul8 on the LifeGuide Platform. Invite reply data will be entered into the Research Team databases locally. Participant screening data will be collected by telephone and entered into MACRO by the study site staff. Baseline data will be collected prior to randomisation. Baseline and outcome data will be patient self-completed on a separate data collection section of the Regul8 website (as was carried out successfully for the MIBS study), away from the study team, thus avoiding any influence of the study team on the responses and reducing bias. This website will be maintained by the computer support team at Southampton, which is hosting the website. Participants will be given a unique password to log onto the website. Their data will be identified by a unique identification number and will be kept separate from any personal identifying data, to maintain confidentiality. A Therapist database on the CTU MACRO system will be completed by the therapists. It will record which therapist provided the sessions, number of sessions and other contact telephone calls, any drop outs from therapy and a therapist-recorded rating of patient change, adherence and acceptance of therapy model.

### Baseline measures

The screening questionnaire will capture baseline data including Rome III questionnaire, duration of IBS, type, previous CBT, medications previously taken for IBS, and inclusion and exclusion criteria. The participant will complete an online baseline assessment questionnaire, which includes the outcome measures detailed below plus sociodemographic details, current medication, medical history and medications, duration of IBS symptoms and previous or current psychiatric diagnoses.

### Outcome measures

Outcome data and questionnaires will be completed at baseline, 3, 6 and 12 months after randomisation, by all participants. Participants will be sent a reminder email at 3, 6 and 12 months, to prompt them to complete entering the data 1 week prior to the questionnaire due date. If it has not been completed within 1 week of the reminder, a further two reminders will be sent. One week after that, if no data have been entered, the research team will ring the participant to ask if they can collect the data by hard copy or over the telephone. 90% follow-up was achieved (at 12 weeks) by this method in the MIBS trial, which collected very similar baseline and outcome measures to those proposed for this study.

### Primary outcomes: IBS-SSS and WASAS

IBS Symptom Severity Score (IBS SSS)^23^ is widely used in IBS studies. It is a five item self-administered questionnaire measuring: severity of abdominal pain, duration of abdominal pain, abdominal distension/tightness, bowel habit and quality of life. (Maximum score 500: <75 normal bowel function, 75–174 mild IBS, 175–299 moderate IBS, 300–500 severe IBS). A 50 point change from baseline is regarded as clinically significant.^23^

The Work and Social Adjustment Scale (WASAS) measures the effect of the IBS on people's ability to work and manage at home, participate in social and private leisure activities, and maintain relationships.^24^ WASAS has been shown to be sensitive to change in IBS trials.^6^
^16^ It has five aspects scored 0 (not affected) to eight (severely affected), total possible score 40.

### Secondary outcome measures

Two of the secondary outcomes will not be completed at baseline, only at follow-ups These include the SGA (Subject's Global Assessment of Relief)^25^ and the Patient Enablement Questionnaire.^16^

The SGA is frequently used in treatment trials to identify IBS responders to therapy.^25^ Participants rate their relief from IBS symptoms on a scale of 1–5 ranging from ‘completely relieved’ to ‘worse’. Scores are dichotomised so that patients scoring from 1 to 3 are considered responders and those scoring 4–5, non-responders.

The Patient Enablement Questionnaire^27^ assesses change in the participants’ ability to cope with their illness and life after treatment.

Mood will be measured by the Hospital Anxiety and Depression Scale (HADS),^28^ a well validated, commonly used, self-report instrument for detecting depression and anxiety in patients with medical illnesses.

The acceptability of the self-management treatment will be assessed using questions where patients rate the overall effectiveness of the programme, the efficacy of programme compared to other treatments they have tried and whether they enjoyed the programme.

The Client Service Receipt Inventory (CSRI)^29^ and EQ-5D^26^ will be used to gather information on use of health services, and health-related quality of life, respectively. The CSRI has been adapted for use in many economic evaluations and has been used in previous IBS evaluations. The EQ-5D is the most frequently used tool for generating quality-adjusted life years (QALYs), which are favoured by NICE.

### Adherence to therapy

Patients’ adherence to the treatments will be measured through recording the number of phone sessions and an automated count of web sessions accessed. Completing four or more sessions of the website and one or more of the telephone support calls will be deemed as compliant with the website. In the TCBT arm, completing four or more of the initial telephone CBT sessions will be deemed as compliant.

Any modifications or departures from randomised treatments, and withdrawal of participants from trial treatment or research follow-up, will be recorded and reported as such.

### Putative mediator variables

Mediator variables include cognitions and behaviours that form part of the cognitive behavioural treatment model and are targets of the therapies.

These include

Cognitive Scale for Functional Bowel Disoders (CG-FBD),^30^ a 31 item scale assessing unhelpful cognitions related to IBS.

Brief Illness Perception Questionnaire for IBS (IPQ),^31^ consisting of an eight point scale to assess participants perception of their illness.

The Belief about Emotions Scale (BES),^33^ a 12-item questionnaire that measures beliefs about the unacceptability of experiencing and expressing negative emotions. These beliefs are likely to have implications for emotion regulation and processing.

The Irritable Bowel Syndrome-Behavioural Responses Questionnaire,^32^ a 26 item scale that measures changes in behaviour specific to managing IBS symptoms.

The “Impoverished Emotional Experience (IEE)” factor of the Emotional Processing Scale,^34^ which is composed of five items, and relates to the labelling and awareness of emotional events that influence the way people process their emotions.

The Positive and Negative Affect Schedule (PANAS),^35^ which measures both positive and negative affect. The current results indicate that positive and negative effect are relatively independent dimensions. Participants will complete only the positive effect subscale because the HADS scale will already measure negative effect.

### GP notes review

Patients’ GP notes will be reviewed at 12 months to assess GP and other consultations in the year prior to entering the study and in the 12 months since entry into the study. Other studies have shown an impact on GP contacts from patient self-management programmes.^16^
^37^

### Qualitative component

A nested qualitative study will explore patients’ experiences of treatments. The objectives of this study are: to identify factors that facilitate or impede adherence to web-delivered and therapist-delivered CBT; to provide insight into the quantitative results; and to explore social and psychological processes of change. Semistructured interviews will be conducted at 3 and 12 months, with approximately 17–20 participants per arm (ie, 10–12%, sampled purposively to encompass a mix of gender and ages, and a range of baseline symptom severity scores). Interviewers will use topic guides comprising open-ended questions and prompts designed to elicit participants’ accounts of their experiences of IBS in relation to the trial. Interviewing participants from each active arm will enable us to identify factors related to adherence and change processes; including participants from the TAU arm will provide insight into the quantitative results. Interviewing the same participants at 3 and 12 months will allow us greater depth to explore change processes over time and provide the potential to understand better any differences in the quantitative results between 3 and 12 months. Interviews will be transcribed verbatim. Analysis will begin on completion of the first few interviews and will proceed iteratively, thus allowing early insights to be explored more fully in later interviews and topic guides to be modified if necessary. Inductive thematic analysis,^38^ employing supplementary techniques from grounded theory,^39^ will be used to code the data and to identify themes that capture key concepts and processes. To enhance quality: multiple researchers will contribute, to avoid producing idiosyncratic interpretations; a ‘member check’ will be conducted whereby interviewees will be invited to comment on summaries of their interviews; and an audit trail (coding manual and notes) and interviewers’ field notes will be produced. The qualitative results will thus provide insights into the relative merits of each type of CBT and identify delivery issues to attend to in any future widespread implementation.

### Proposed sample size

Sample size was based on the two primary outcomes, IBS-Symptom severity score (IBS-SSS)^23^ and WASAS.^24^
^40^

A 35 point difference between therapy groups and TAU on IBS SSS at 12 months is regarded as clinically significant (assuming a 15 point placebo response in the TAU arm in the trial).^23^ Assuming a within-group IBS SSS standard deviation (SD) of 76 points (taken from MIBS pilot study^14^), this equates to an effect size of 0.46. To achieve 90% power to detect such an effect or larger using a two-sided independent samples t test at the 2.5% significance level (adjusting for 2 primary outcomes), would require 119 subjects per group. Based on each of 10 therapists delivering therapy to 17 patients within WBCBT and TCBT groups, and an intraclass correlation of 0.02, taken from Baldwin,^41^ this sample size needs to be increased by an inflation factor of 1.32, to take account of therapist effects. We will measure IBS SSS at baseline and assume that baseline values are predictive of post-treatment values (correlation 0.4). Accounting for this in our statistical analysis model allows us to decrease the sample size by a deflation factor of 0.84. Finally, assuming that attrition will be less than 20%, we apply a further inflation factor (factor 1.25) to allow for this. The final sample size requirement is 165 patients per group, or 495 patients in total.

In terms of our second primary outcome (WASAS), this sample size would be sufficient to detect a clinically important difference between the WBCBT (or TCBT) and TAU groups in the WASAS. Specifically, we can assume inflation factors of 1.32 for correlation of outcomes within therapists, and of 1.25 for attrition and a deflation factor of 0.84, for correlation between baseline and follow-up measures. Therefore, a moderate effect size of 0.46 could be found with 90% power at the 2.5% significance level, given 119 participants per group. Assuming a SD of 8.0 (as estimated in a study of CBT for IBS^6^), this would equate to a clinically meaningful treatment difference of 3.7 points on this scale. This is less than the difference of 5.4 points in change of means that was found in a trial of a CBT-based self-management intervention for IBS.^16^

### Statistical analysis

The Statistical analysis plan has been approved by the trial steering committee. The aim is to evaluate effectiveness, and all analyses will follow the intention-to-treat principle. Group differences on the primary IBS-SSS outcome will be assessed using a mixed linear regression model for repeated measurements. In this model, IBS-SSS at post-treatment time points (3, 6 and 12 months) will feature as the dependent variable. Explanatory variables will be baseline IBS-SSS, treatment group, IBS symptoms type, stratifier (centre) and time and time by treatment interaction terms to allow for different group differences at the various assessment time points. (The assessment time point of primary interest is 12 months. The modelling provides the treatment effect estimates at the 12 month time point as well as for further post-treatment secondary time points). Correlation between repeated measures of the same participant or between participants, or due to sharing the same therapist, will be allowed for by including subject-varying random intercepts as well as therapist-varying random intercepts for TCBT and WBCBT groups in the mixed models. Mixed models account for missing outcome data under the missing at random assumption. The effect of departures from this assumption will be checked using sensitivity analyses.^42^ WASAS scores will be analysed using mixed models in a manner similar to the analysis of IBS-SSS. Secondary outcomes, including Subjects’ Global assessment of relief (SGA), EQ-5D, Enablement, HADS, Brief Illness perception Questionnaire (IPQ), Cognitive Scale for Functional Bowel disorders, The Belief about Emotions Scale (BES), The “Impoverished Emotional Experience (IEE)” factor of the Emotional Processing Scale, The Positive and Negative Affect Schedule (PANAS), adverse events (AEs) and healthcare utilisation, are important to measure the wider IBS effects and will be analysed similarly (as appropriate for continuous or dichotomous outcomes). A complier average causal treatment effect will be estimated using instrumental variable methods to assess efficacy if there is appreciable lack of compliance.^43^

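### Subject random intercepts, with default residuals, tie the 12-month standard error to a variance averaged over 3, 6 and 12 months; an unstructured three-visit covariance removes that risk cheaply

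*Protocol article*

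**What the plan says.** All of the following is in the Statistical analysis section of the Protocol article.

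- Group differences on IBS-SSS "will be assessed using a mixed linear regression model for repeated measurements", and "IBS-SSS at post-treatment time points (3, 6 and 12 months) will feature as the dependent variable".
- The means are free to differ by visit through "time and time by treatment interaction terms to allow for different group differences at the various assessment time points".
- Correlation "will be allowed for by including subject-varying random intercepts as well as therapist-varying random intercepts for TCBT and WBCBT groups in the mixed models". The section names no random slope, visit-specific residual variance, unstructured matrix or robust standard error, and it does not state the residual structure.
- "The assessment time point of primary interest is 12 months".
- "Mixed models account for missing outcome data under the missing at random assumption", with sensitivity analyses for departures from that assumption.
- For the second primary outcome, "WASAS scores will be analysed using mixed models in a manner similar to the analysis of IBS-SSS".

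The same section says that an approved SAP exists. It is not at hand. The Proposed sample size section sets the 2.5% two-sided level for the two primary outcomes and gives one IBS-SSS SD, 76, with no variance or correlation by visit.

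**The concern.** A subject random intercept with independent, constant-variance residuals is compound symmetry. The variance is the same at every visit, and the correlation is the same for 3 with 6 months, 6 with 12 and 3 with 12, which are gaps of 3, 6 and 9 months. The therapist intercepts add only a constant in the two therapy arms, so they do not change this pattern.

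The design gives some reason to doubt equality. Therapy lasts 9 weeks, with boosters at 4 and 8 months (Planned interventions). The 3-month visit therefore follows the main course closely, 6 months lies between the boosters, and 12 months comes four months after the last one. The model lets the mean differ at each visit but holds the spread fixed.

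Two things are at stake. The 12-month standard error, which drives the confidence interval and test for both primary outcomes, would be based on a variance pooled over visits. And under missing at random, the model uses earlier visits to inform missing 12-month values through the assumed covariance, so a wrong covariance can shift the estimate when dropout is selective. The planned sensitivity analyses are aimed at departures from missing at random, not at this assumption.

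**Working it through.** **The plan's own figure.** Difference 35, SD 76, two-sided 2.5%, 90% power: the noncentral t calculation gives 119 per group (power 0.902). Then 119 × 1.32 × 0.84 × 1.25 = 164.9, or 165 per group. The sample size reproduces and is not affected by this point.

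**Complete data, by hand.** With all three visits observed and a treatment effect at each visit, the 12-month contrast depends on the 12-month data alone. Its true variance is proportional to SD₁₂². The random-intercept model uses the average of the three visit variances instead. So

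- ratio r = model SE / true SE = √[(SD₃² + SD₆² + SD₁₂²)/3] / SD₁₂
- actual type I error = 2 × [1 − Φ(2.2414 × r)], where 2.2414 is the two-sided 2.5% critical value.

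The SDs stand for spread after baseline adjustment. The ratio is unchanged if baseline explains the same share at each visit. The visit patterns are assumptions centred on the one SD given.

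| Assumed SD at 3/6/12 months | Mean variance | r | Actual error at 2.5% |
|---|---|---|---|
| 76/76/76 | 5776.0 | 1.000 | 2.5% |
| 72/76/80 | 5786.7 | 0.951 | 3.3% |
| 70/76/84 | 5910.7 | 76.88/84 = 0.915 | 4.0% |
| 84/76/70 | 5910.7 | 76.88/70 = 1.098 | 1.4% |

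**Therapist effects.** Take the article's ICC of 0.02 and 10 therapists: therapist variance 0.02 × 76² = 115.5, adding 11.55 to the variance of the therapy-arm mean. For 70/76/84 the model variance of the difference is 11.55 + 2 × 5910.7/165 = 83.2, and the true variance is 11.55 + 2 × 7056/165 = 97.1. Then r = √(83.2/97.1) = 0.926 and the error is 3.8%. The effect is diluted a little, not removed.

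**With dropout, by simulation.** REML fits, 165 per arm, two arms, baseline-adjusted, no therapist effects, 700 to 1,000 runs. Assumed dropout depends on the last observed score, in opposite directions in the two arms. The correlations between the follow-up visits are also assumed: 0.70, 0.50 and 0.65 for 3 with 6, 3 with 12 and 6 with 12 months, except in the last row. At a true 2.5%, the Monte Carlo SE of the error rate is about 0.5 to 0.6 percentage points.

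| Scenario | Random intercept: SE ratio, error, bias | Unstructured: SE ratio, error, bias |
|---|---|---|
| 70/76/82, no dropout | 0.93, 3.9%, −0.2 | 1.02, 2.8%, −0.2 |
| 70/76/82, dropout | 0.88, 4.7%, −0.4 | 0.99, 2.0%, 0.0 |
| 64/76/88, dropout | 0.83, 6.6%, −1.6 | 0.99, 2.1%, −0.3 |
| Equal SDs, decaying correlation, dropout | 0.95, 3.0%, 0.8 | 0.99, 1.9%, 0.3 |
| Compound symmetry true, dropout | 1.00, 2.7%, −0.2 | 0.99, 2.9%, −0.2 |

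The first row agrees with the hand formula: √5800/82 = 0.929, error 3.7%. The largest bias, 1.6 points, is about 4.5% of the 35-point target. In the last row the empirical SEs are 8.27 and 8.30, so the unstructured fit loses 8.30/8.27 − 1 = 0.4%.

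**The case against.** The strongest objection is that the article never says the residuals are independent with constant variance. A random intercept with visit-specific residual variances fits the same sentence and would remove the equal-variance problem. An article may leave residual structure to the SAP, and its absence is no fault. This stands as a limit on the claim: compound symmetry is implied under the usual default, and is not stated. It does not dispose of the point, because the article makes a positive choice of device for within-participant correlation, and as written that choice leads most readily to the default model.

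Next, nothing in the article shows that spread or correlation differs by visit. This also stands. A reader might infer that the primary tests are anti-conservative. The article does not support that: falling SDs make the test conservative, at a cost in power, and equal SDs with equal correlations leave it correct.

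Third, the simulated bias depends on a dropout pattern that the article does not describe. It describes email reminders and a follow-up call (Outcome measures), and blinded telephone capture of the primary outcome (Blinding). The bias should be read as possible and small. With equal SDs, the simulated error of 3.0% is within Monte Carlo error of 2.5%.

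Finally, it is tempting to say that an unstructured covariance costs nothing. It costs little, but it uses more parameters and must be fitted alongside therapist effects that exist in only two of the three arms.

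**Conclusion.** The point holds as a cheap improvement to a stated choice, not as an error in the plan. If the residuals are independent with constant variance, and if variances or correlations differ across 3, 6 and 12 months, the 12-month standard error for IBS-SSS and WASAS can be wrong in either direction. Over the complete-data SD patterns above, actual error runs from about 1.4% to 4.0% against 2.5%. With assumed selective dropout, the more extreme pattern reached 6.6% and a bias of about 1.6 points. All of these sizes rest on assumed visit-specific SDs, correlations and dropout; the article supplies only the SD of 76. The asymmetry decides the matter: the unstructured fit kept the standard error within about 2% of the truth in every scenario and lost about 0.4% when the simpler structure was true. A baseline-by-time term and the degrees-of-freedom method are optional SAP detail and form no part of this point.

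**What to change.** For both primary outcomes, replace the subject random intercept with an unstructured within-participant covariance over the three post-baseline visits, and keep the therapist random intercepts in the two therapy arms. The subject intercept must be dropped and not kept beside the unstructured matrix, because the two cannot be separately identified. Pre-specify a fallback if the model does not converge: heterogeneous compound symmetry first, then the random intercept. Settle this before unblinding, so that the covariance is not chosen on the results. If the SAP already specifies such a structure, it is enough to align the article's description with it.

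Cost: a sentence in the SAP and a small change in code, six within-participant covariance parameters in place of two, about 0.4% in standard error if compound symmetry is true, and a slightly higher chance of non-convergence, which the fallback covers.
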